| Objectives | Primary:   - To examine how a magnetic marker compares to the guidewire in successful lesion localisation, minimal excess tissue removal and negative margins in surgery of non-palpable breast lesions. - To evaluate the combination of a ferromagnetic marker for tumour localisation with Superparamagnetic Iron Oxide Nanoparticle (SPIO) for sentinel lymph node detection (SLND) in early breast cancer treatment.   Secondary:   - To evaluate operative times and logistical efficacy of magnetic markers compared to guidewire in the above setting. - To evaluate patient as well as physician satisfaction with the use of this totally magnetic technique. - To evaluate patient quality of life (QoL) |
| Study Design and Methods | Multicentre Pragmatic Randomized Controlled Trial: Patients with confirmed non-palpable ductal cancer in situ (DCIS) or invasive breast cancer, planned for breast conserving surgery (BCS) and SLND will be randomized in two arms.  Arm 1: Lesion localisation with magnetic marker  Arm 2: Lesion localisation with guidewire  Axillary mapping will be done in both arms with the use of SPIO (1-1.5ml Magtrace ©, Endomag, Cambridge,UK) . In the interest of a pragmatic trial, lesion localisation with a magnetic marker as well as SPIO injection will be performed by either a breast surgeron or a radiologist and within a 14 day window before the operation according to local routines or case-per-case convenience. SPIO will be administered peritumoraly. Guidewire localisation will always be performed by a breast radiologist on the day or at most one day before surgery. All cases of localisation will be performed under local anesthetic.  The performing surgeon will document all relevant data in a case reporting form.  All patients will be followed up for postoperative complications, need for re-excision and QoL assessment for 2 years. QoL assessment will be done via PROs questionnaires and the patients experience will be evaluated with PREMs questionnaires.  All involved disciplines (surgeons, radiologists, co-ordinators) will rate their experience with each technique with Likert scale items. |
| Primary Endpoints | To examine the equivalence of magnetic marker and guidewire in successful localisation of non-palpable breast lesions by comparing:   - Re-excision rate - Resection ratio - Sentinel node detection rate |
| Secondary Endpoints | - Adverse events - Operative time - PROs and QoL evaluation - PREMs and cost- effectives analysis |

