**2.2 Objectives**

**2.2.1 Primary Objective**

1. The primary objective is a composite of the three components of successful breast conserving surgery for early breast cancer. These components include the re-excision rate, minimal excess tissue removal, and successful SLN detection. The aim of this trial is to compare these three variables between the two arms.

The hypotheses to be tested are:

1. Magnetic marker lesion localization is not equivalent to guidewire localization in terms of re-excision rates due to inadequate surgical margins. Adequate margins are considered “no tumour on ink” for invasive cancer and 2 mm for pure DCIS and will be assessed by specialized breast pathologists.

2. Magnetic marker lesion localization is not equivalent to guidewire localization in terms of excess tissue removal. This will be expressed as the resection ratio and will be assessed by the ratio of the Optimal Resection Ratio (ORV) to the Actual Resection Ratio (ARV).

- ORV will be calculated for each tumour based on the radiological dimensions of the tumor (in cases of discordance between different modalities, the largest dimension will be used) using the volume calculation formula for ellipsoid tumours
[figure not shown]
, where *r*1= x radius +1cm, *r*2=y radius+1cm, *r*3= y radius +1cm. In all dimensions, 1 cm is added as it is the universally accepted macroscopic margin for breast lesions^26^.

ARV will be calculated based on the specimen weight.

Optimally, the ratio $\frac{ARV}{ORV}$ should be as close to 1 as possible to ensure that no unnecessary tissue is removed which may jeopardize the cosmetic and functional outcomes of a breast conserving operation.

3. The combination of magnetic markers and SPIO is not equivalent to the combination of a guidewire and SPIO for SLN detection.

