**3.Methods**

**3.1 Patient Recruitment and Consent**

Patients will be informed about the study during their first visit to the outpatient breast clinic after being informed about their diagnosis and surgical plan. Given the delicate nature of the diagnosis, adequate time will be given to the patients to process the information and when indicated, a second visit will be planned to give them more information about their diagnosis, the proposed treatment plan, and, eventually, their participation in the study. All patients who are interested in the study will be given a patient information form that they can keep and a patient consent form in which they can opt for being sent a copy of the published data of the study. Patients may decide to withdraw from the study at any point before localization is performed.

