**3.2 Data collection**

The data collected included baseline patient and tumor characteristics, intraoperative details, and postoperative data including the pathology report, report of complications, and SPIO-induced skin staining.

Preoperative data:

- Age, Sex, BMI
- Radiographic tumour size and BIRADS (both mammogram and Ultrasound)
- Optimal resection volume
- Tumour location (side, quadrant, distance from nipple areola complex)
- Clinical size
- Preoperative core biopsy, needle size
- Histology, grade and receptor status
- Date of SPIO injection, US guided or not and volume
- Date of tumor localization, method employed, radiological guidance, time, and complications of the procedure.

Intraoperative data:

- Date of primary surgery
- Type of procedure
- Sentimag counts in breast and axilla after induction of anaesthesia
- Time from skin incision to specimen excision
- Radiologic margins (min, max)
- Skin excision information
- Sentimag counts on specimen and background
- Specimen weight
- Tracer or tracers that are used
- Successful SPIO SLNB
- Successful SLNB by any method
- Number of SLN
- Axillary procedure

Postoperatice data

- Date of pathology report
- Date answer was delivered to patient
- Specimen dimensions
- Histology and grade
- Size
- Receptor status
- Margin status and closest margin
- SLN number, number of metastases if any in SLN
- Skin staining and size
- Residual magnetic signal
- Planned reoperation
- Breast specific complications within 30 days, CD and CCI grading
- BREAST-Q preoperative, expectations, immediate postoperative, 6 months postoperative, 12 months postoperative

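### The resection ratio sets the weight of everything in the specimen against tumour plus 1 cm, so it mixes type of procedure with localisation accuracy; the likely cost is added variance and blurred meaning

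*Protocol*

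**What the plan says.** Section 2.2.1 (hypothesis 2) defines the resection ratio, one of three primary endpoints.

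- **Denominator (ORV):** an ellipsoid built on the radiological tumour radii. "In all dimensions, 1 cm is added as it is the universally accepted macroscopic margin for breast lesions".
- **Numerator (ARV):** "ARV will be calculated based on the specimen weight". No deduction is stated for skin or for tissue taken because of the type of operation.
- **Reading:** the ratio "should be as close to 1 as possible to ensure that no unnecessary tissue is removed". The stated reason is the cosmetic and functional result.

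The Summary table, under Primary Endpoints, gives the ratio a second role: "To examine the equivalence of magnetic marker and guidewire in successful localisation of non-palpable breast lesions by comparing" three measures, of which it is one.

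Section 3.2 lists "Type of procedure" and "Skin excision information" among the intraoperative data, with a single item for "Specimen weight". Nothing links the first two to ARV. Section 2.7 names Student's t-test or the Mann-Whitney test for continuous variables and no covariate. Section 2.6 plans for a difference of 0.3 in the ratio (1.8 against 1.5), two-sided 0.05 and 80% power, and gives no SD. Section 3.1 has patients informed of the study "after being informed about their diagnosis and surgical plan".

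**The concern.** The two halves of the ratio do not cover the same tissue. ORV is fixed by the tumour and the margin. ARV takes in whatever is in the specimen. If the operation removes skin, or parenchyma beyond the margin by design, the ratio rises although the lesion was found exactly where it should be. The protocol anticipates variation of this kind, since it records procedure type and skin excision, sets no limit on the type of breast-conserving procedure, and admits T1-T3 tumours.

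Two things are at stake. Spread that has nothing to do with the marker makes a difference of 0.3 harder to detect. And a ratio well above 1 cannot be read as a localisation result without knowing which operation was planned.

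**Working it through.** The protocol states no sample size and no SD for the ratio, so there is no planned figure to reproduce. What follows is a sensitivity calculation.

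**Inputs from the protocol:** 1 cm added to each radius (2.2.1); difference 0.3, two-sided 0.05, power 80% (2.6).

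**Assumptions:** spherical tumour; 1 g = 1 cm³; base SD 0.8; a share p of patients carrying an extra ratio e from planned tissue, equally in both arms. The ellipsoid formula is a figure not shown, so the standard form is used.

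**Step 1. How much tissue is 0.3?** ORV = (4/3)π(d/2 + 1)³, d in cm.

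| Tumour | ORV (cm³) | 0.3 × ORV (cm³) | Ratio added by 10 g | Ratio added by 50 g |
|---|---|---|---|---|
| 10 mm | 14.1 | 4.2 | 0.71 | 3.54 |
| 15 mm | 22.4 | 6.7 | 0.45 | 2.23 |
| 20 mm | 33.5 | 10.1 | 0.30 | 1.49 |
| 30 mm | 65.4 | 19.6 | 0.15 | 0.76 |

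**Step 2. Skin alone.** Volume = (π/4) × length × width × thickness. Assumed ellipses from 3 × 1 × 0.15 cm to 6 × 3 × 0.2 cm give 0.35 to 2.83 cm³. Divided by 22.4 this adds 0.02 to 0.13 for a 15 mm tumour; divided by 14.1 it adds 0.03 to 0.20 for a 10 mm tumour. Skin is the smaller contribution.

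**Step 3. Power with the extra tissue balanced between arms.**
n per arm = 2(1.96 + 0.84)² × 0.8² / 0.3² = 112 after rounding up.
SD with extra tissue = √(0.8² + p(1 − p)e²).
Power = Φ(0.3 / (SD × √(2/112)) − 1.96).

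- e = 2, p = 5%: SD = √(0.64 + 0.19) = 0.91; power 69%.
- e = 2, p = 20%: SD = √(0.64 + 0.64) = 1.13; power 51%.
- With SD 1.0 and 175 per arm instead, and p = 20%: e = 0.3 leaves 79.6%, e = 1 leaves 74%, e = 2 leaves 59%.

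**Step 4. The tests named in 2.7, and adjustment.** Simulation with a normal base, SD 0.8, 112 per arm and 4,000 runs per row. The adjusted analysis is a linear model with arm and the pre-allocation procedure indicator.

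| e | p | t-test | Mann-Whitney | Adjusted model |
|---|---|---|---|---|
| 2 | 5% | 70% | 72% | 80% |
| 2 | 20% | 51% | 53% | 79% |
| 4 | 5% | 47% | 68% | 79% |
| 4 | 20% | 23% | 45% | 80% |

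At e = 4 the normality check in 2.7 would send the analysis to Mann-Whitney, so its column is the fair one there. The adjusted column assumes that the recorded plan identifies the extra tissue exactly; in practice the recovery would be smaller.

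**The case against.** **No bias is shown.** A reader might infer that procedure mix can mask or mimic a marker effect of about 0.3. The documents do not support that. The surgical plan is set before recruitment, and allocation is 1:1 in concealed envelopes, so planned tissue is balanced in expectation when patients are compared as randomised. Chance imbalance is real (at 112 per arm and 5-20% prevalence, the standard error of the difference in prevalence is 2.9-5.3 points), but it is already inside the inflated SD of Step 3 and must not be counted again. Choosing skin or procedure by arm is possible in an open-label trial, and the April 2020 amendment lets localisation be chosen regardless of assignment. Neither is evidence that it happens. This objection stands.

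**The planning may already contain this variance.** The planning ratios come from the pilot and the literature. If those used whole-specimen weights, their spread includes it. No SD is stated, so this cannot be settled either way. It stands.

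**Total tissue removed is a legitimate outcome.** Section 2.2.1 justifies the ratio by cosmetic and functional results, for which total weight is relevant. Skin taken may also be part of the technique's effect, since the probe guides incision placement (1.2.3). This is a good reason to keep whole-specimen weight as the primary measure. It does not remove the difficulty that the Summary presents the same ratio as evidence on localisation.

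**Subtracting reshaping tissue would be worse.** An unblinded surgeon would then decide after allocation which tissue counts. This also stands, and it shapes the fix.

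**Density.** One conversion constant scales both arms alike and leaves the t and Mann-Whitney tests unchanged. It is a minor clarification only.

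**Adjustment may be in an SAP that is not shown.** That is possible. But ARV is defined in the protocol, and an SAP cannot adjust for a planned procedure type that was not recorded before allocation; section 3.2 lists procedure type only among the intraoperative data.

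**Conclusion.** The definitional point holds. Whatever is in the specimen enters ARV, ORV allows only tumour plus 1 cm, and the items that would separate procedure from localisation are collected but not used. The consequence is added variance and a blurred reading of the endpoint, with no demonstrated difference between arms.

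Its size cannot be fixed from the documents. Under the stated assumptions, a few grams matter for small tumours (6.7 cm³ equals 0.3 at 15 mm), and power falls from 80% to about 69-51% if 5-20% of patients carry an extra ratio of 2. If the extra is only 0.3, the loss is negligible. Larger losses obtained from the t-test at an extra ratio of 4 overstate the case, because the protocol's own Mann-Whitney route gives about 68-45%. The protocol does not say how often planned tissue is removed or how much it weighs. This is a worthwhile, inexpensive improvement. It does not show that the endpoint is invalid.

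**What to change.** 1. **Section 2.2.1:** keep ARV as the weight of the whole specimen, say so explicitly, and state one conversion to volume. No tissue is to be left out of the primary ARV by judgement after allocation.
2. **Section 3.2:** add one preoperative field, completed before the envelope is opened, for planned procedure type (standard excision, or excision with additional planned tissue removal).
3. **Section 2.7:** replace the unadjusted comparison of the resection ratio with one adjusted for that baseline field: a linear model with arm and planned procedure type, or a rank test stratified by it if the distribution requires. Use the planned type; the procedure actually performed is known only after allocation.
4. **Sensitivity analyses:** (a) ARV with skin subtracted, using the skin-excision data already collected (confirm that the form records dimensions, and state a thickness); (b) patients planned before randomisation for standard excision only.

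Cost: one extra field before randomisation and a little more analysis, with no extra patients and no change to care. Tissue added by decisions during surgery stays in ARV and is not adjusted for. That is the price of an objective measure.

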**2.2.2. Secondary Objectives**

1. Evaluation of the frequency of adverse events, that is, failed localization and postoperative complications, with each method.

2. Time to specimen and total operative time for each technique.

3. The evaluation of healthcare personal experience with each technique via Likert scale items

4. Evaluation of patients’ QoL through PROs and their experience with each technique via PREMs questionnaires.

5. Cost-effectiveness analysis for each technique.

**2.3 Patient Population and Indications**

**2.3.1 Inclusion Criteria**

1. Patients aged ≥ 18 years

2. Patients with DCIS or invasive breast cancer (T1-T3) requiring localisation planned for primary surgery including sentinel node biopsy

**2.3.2 Exclusion Criteria**

1. Intolerance/hypersensitivity to iron or dextran compounds.

2. Patients with iron-overload disease.

3. Patients with pacemakers or other implantable devices in the chest wall or prosthesis of the shoulder.

4. Patients deprived of liberty or under guardianship.

5. Pregnant or lactating patients.

6. Inability to provide informed consent.

**2.4 Study Design**

The study is designed as a randomised controlled trial that complies with the principles of pragmatism. The extent of pragmatism was quantified using the PRagmatic-Explanatory Continuum Indicator Summary 2 (PRECIS-2) score, a tool used to facilitate the design of pragmatic trials^27^.PRECIS-2 evaluates the applicability of a trial within 10 domains and produces a PRECIS-2 wheel, as shown in the table below.

**Table:** **PRECIS-2 scores for trial domains**

| **Domain** | **Score** | **Rationale** |
| --- | --- | --- |
| Eligiblity criteria | 5 | Patients with breast tumours that need localisation- Exclusion criteria related to reaction to the material and not the delivery of the technique. |
| Recruitment Path | 5 | Recruitment performed during routine clinic appointment for surgery planning. |
| Setting | 4 | Study conducted in two university and one county hospital, with various case volumes and level of experience. However, all three centres are in the same country. |
| Organisation intervention | 5 | No prior training or additional resources needed for and of the disciplines involved in the trial. |
| Flexibility-delivery | 5 | No monitor or specific advice on co-intervention. |
| Flexibility -adherence | 5 | No special adherence measures. |
| Follow up | 4 | A 2 year follow up which is not routine in usual care and QoL measurements. |
| Outcome | 5 | Primary outcomes are directly relevant to participants |
| Analysis | 5 | All available data used |

PRECIS-2 wheel

Patients with non-palpable DCIS or invasive breast cancer confirmed by fine-needle aspiration (FNA), core biopsy, or vacuum-assisted biopsy (VAB), which are planned for BCS and SLND, will be asked to participate in the trial. Upon their consent, they will be randomized to either arm 1 (lesion localization with magnetic marker) or arm 2 (lesion localization with guidewire).

**2.5 Localisation Technique**

The magnetic marker that will be used is Magseed© (Endomag, Cambridge,UK). All patients will receive peritumoral SPIO (1-1.5 ml Magtrace©) up to 14 days before surgery. SPIO administration and magnetic marker insertion may be performed by either a radiologist or breast surgeon, but always with radiological guidance. SPIO will be injected in the dorsal surface of the tumor while the magnetic marker will be placed on the ventral surface of the tumour. Guidewire placement will be performed exclusively by a breast radiologist as per routine, with the tip of the guidewire advancing approximately 1 cm past the lesion to ensure adequate macroscopic margins.

All specimens will be sent to the radiology department after excision and orientation to ensure that the tumor and marker are within the specimen. The radiological margins will be documented.

The trial is open to all breast radiologists and surgeons regardless of their level of experience or familiarity with the technique to ensure that the results are applicable to any clinical setting.

**2.6 Sampling and Data Analysis Plan**

The sample size is calculated based on the principle of equivalence, allowing for the detection of a significant difference in resection ratios of 0.3 adjusted for a non-inferiority margin of 4% for re-excision rates and SLN detection. The literature suggests a resection ratio for the guidewire between 2-2.8. To obtain robust results, we lowered that to 1.8 and accepted a 1.5 resection ratio for the totally magnetic technique stemming from our previous pilot study ^25^. Two-sided p-value is set at 0.05 and power to 80%. An additional 10% to sample size calculation will be recruited as inflation to pragmatic settings and tolerance.

The participants will be randomized with an allocation ratio of 1:1 in blocks of 8. The R-Randomizer package will be used for the randomization. The allocated arms will be in dark envelopes, and neither of the involved disciplines will be able to know the arm in which the participants will be randomized beforehand. All participants will receive a code upon randomization consisting of the first three letters of the recruiting center and a number that will be consecutive. The data will be collected by appointed research coordinators.

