**2.Investigational Plan**

**2.1 Title**

Magnetic marker or guidewire localization of non-palpable breast cancer in combination with magnetic sentinel lymph node dissection. An open-label, phase 3, pragmatic, randomized controlled trial.

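### A single, disclosed block size of 8 in an open-label trial does not secure the statement that nobody can know the arm beforehand

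*Protocol*

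**What the plan says.** Protocol section 2.6 fixes the scheme: "The participants will be randomized with an allocation ratio of 1:1 in blocks of 8". It names the tool ("The R-Randomizer package will be used for the randomization") and describes concealment as follows: "The allocated arms will be in dark envelopes, and neither of the involved disciplines will be able to know the arm" in advance. Each participant then receives "a code upon randomization consisting of the first three letters of the recruiting center and a number that will be consecutive".

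Section 2.1 describes the study as "An open-label, phase 3, pragmatic, randomized controlled trial". The PRECIS-2 table in section 2.4 gives the setting: "Study conducted in two university and one county hospital". The text after that table places consent before randomisation.

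The protocol does not say that block sizes vary or that the size is withheld from sites. It also does not say whether there is one list or one per hospital, or who holds and opens the envelopes.

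**The concern.** An envelope hides the next assignment. It does not hide what can be worked out from the assignments already opened. With 1:1 allocation in blocks of known length 8, each block holds four of each arm, so once four of one arm have appeared the rest of the block is determined. In an open-label trial, staff see whether a patient was allocated a wire or a marker. The concealment sentence is absolute, and the scheme described does not guarantee it.

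Consent before randomisation does not remove the problem, because the inference comes from earlier patients and is available before the next patient is approached. Section 3.1 places recruitment at an outpatient visit after the diagnosis and surgical plan have been discussed, so the nature of the lesion is known by then. If anyone steered easier or harder lesions towards an arm, the re-excision and resection-ratio comparisons could be biased.

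**Working it through.** The protocol gives no predictability figure, so there is none to reproduce. The inputs are the 1:1 ratio and block size of 8 (section 2.6), the open-label design (section 2.1) and the three hospitals (section 2.4).

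**Case A: the observer sees every allocation in the block** (per-hospital list, or someone who follows the whole sequence).

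A 4:4 block has C(8,4) = 70 equally likely orders. Allocation k is certain if one arm is used up within the first k − 1 places, which has probability 2 × C(k − 1, 4) / 70:

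| Position k | Calculation | Probability that it is certain |
| --- | --- | --- |
| 1 to 4 | – | 0 |
| 5 | 2 × 1 / 70 | 2.9% |
| 6 | 2 × 5 / 70 | 14.3% |
| 7 | 2 × 15 / 70 | 42.9% |
| 8 | 2 × 35 / 70 | 100% |

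The sum is (2 + 10 + 30 + 70) / 70 = 112 / 70 = 1.6 per block, and 1.6 / 8 = 20%. The shortcut 2b/(b + 1) with b = 4 per arm also gives 8/5 = 1.6.

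Guessing the arm with more places left, and tossing a coin at ties, gives 4 + (4⁴/70 − 1)/2 = 4 + (256/70 − 1)/2 = 5.33 correct out of 8, or 66.6%. Enumerating all 70 orders gives the same result.

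**Case B: one list shared by three hospitals, staff seeing only their own patients.**

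Equal hospital size is assumed, so each allocation has a one-third chance of being seen. The observer is also allowed to know where blocks begin, which is generous to the observer. Simulating 300,000 blocks gives about 0.24% certain and 55.5% guessed correctly.

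**Alternatives on a list that is fully seen** (the varying sizes are assumed; the observer knows the set of sizes and guesses optimally):

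| Scheme | Certain | Guessed correctly |
| --- | --- | --- |
| Fixed 8 (current) | 20% | 66.6% |
| Fixed 12 | 14.3% | 64.3% |
| Varying 4/6/8 | about 2% | about 68% |
| Varying 8/10/12 | about 1% | about 65% |

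Varying the size removes nearly all certainty. It lowers the guess rate only if the blocks are not made smaller on average.

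**The case against.** The strongest objection is that 20% is one end of a range. It needs per-hospital lists or full sight of the sequence, and the protocol states neither. On a shared list the exposure at any one site is close to nil. This stands, and it is why both cases are reported.

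Several stronger readings are tempting, but the protocol does not support them:

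- **The participant code proves per-hospital lists or gives the arm away.** The code carries a hospital prefix, but it is given on randomisation and does not encode the arm. The text does not say whether its number runs per hospital. It helps to locate a place in a block only if the numbering follows the list. The envelopes are not described as belonging to hospitals.
- **Allocations in general are predictable.** Even in case A, 80% are not certain, and the first four of each block never are.
- **The recruiting surgeon also operates, so all three primary endpoints are biased.** The protocol does not say who recruits in relation to who operates. The resection ratio is scaled to each tumour's own optimal volume, specialised pathologists assess margins, and both arms receive the same tracer for node detection (sections 2.2.1 and 2.5). These features do not rule out selection effects on re-excision or resection ratio, but they do not allow a claim of bias across all three endpoints.
- **Lack of stratification by hospital is itself an error.** Stratification is a design choice. Adding it would create the per-hospital lists on which predictability is highest.

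The amendment in section 8, which lets the chosen localisation method override the assignment, concerns adherence. It is a separate matter from block predictability.

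**Conclusion.** The point holds in a limited form. The scheme in section 2.6 does not secure its own absolute concealment statement, because a single block size is fixed and disclosed in an open-label trial. On average 20% of allocations are deducible and 66.6% guessable if a full sequence is seen. About 0.24% and 55.5% apply if one list is shared by three hospitals, assumed equal, whose staff see only their own patients. The protocol does not say where the trial lies between these.

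Selection could bias re-excision and resection ratio. A reader might infer that it did, but the protocol contains no evidence of subversion and no basis for estimating the size of any bias. Sample size and power are not affected.

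**What to change.** For patients not yet randomised:

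- Replace the fixed block with randomly varying sizes whose average is not below 8. Sizes 8/10/12 are an example. Sizes 4/6/8 would cut certainty but leave guessing near 68%.
- Keep the sizes out of the protocol and away from recruiting staff.
- Release each allocation only after consent and baseline imaging are recorded. This prevents changes once the arm is known. It does not hide past assignments, so it complements the varying blocks and does not replace them.
- State whether the list is per hospital or shared, and who holds and opens the envelopes. If the list is shared, do not add stratification by hospital without noting that it raises predictability at each site.

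If enrolment is complete, qualify the concealment statement and report the list structure with the results.

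The cost is a new list from the same R tool, a short amendment and a slightly larger possible imbalance at the end. An unfinished block can leave a list unbalanced by up to half its size, so the maximum rises from 4 patients (block of 8) to 6 (block of 12).

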**2.7 Statistical Analysis**

Descriptive statistics will be performed. Continuous variables will be controlled for normality by means of the Kolmogorov Smirnoff and Shapiro- Wilk tests. For normally distributed data, means and standard deviation (SD) will be calculated whereas median with interquartile range (iqr) or range will be used to summarize variables without normal distribution. Detection of significance between groups for these variables will be performed using the Student´s t-test or the Mann-Whitney test**.**

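### No stratification factor is stated and the test named for the resection ratio leaves out centre: a modest, nearly free gain in precision is forgone

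*Protocol*

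**What the plan says.** Section 2.6 of the protocol describes the allocation: patients are "randomized with an allocation ratio of 1:1 in blocks of 8", a randomisation package generates the sequence, and assignments are kept in envelopes. Centre appears there only in the participant identifier: "All participants will receive a code upon randomization consisting of the first three letters of the recruiting center". No stratification factor is named, and the text does not say whether there is one list or one per hospital.

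Section 2.7 covers continuous variables. "Detection of significance between groups for these variables will be performed using the" Student t-test or the Mann-Whitney test, with no centre term. Of the three primary endpoints, only the resection ratio is continuous. No test is named for re-excision or sentinel node detection.

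Three other statements bear on this. The Setting row of the PRECIS-2 table reads "Study conducted in two university and one county hospital, with various case volumes and level of experience". Section 2.5 adds "The trial is open to all breast radiologists and surgeons regardless of their level of experience or familiarity with the technique". Section 2.2.1 defines an adequate margin as no tumour on ink "for invasive cancer and 2 mm for pure DCIS", so the threshold behind re-excision depends on histology.

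For the sample size, section 2.6 gives "Two-sided p-value is set at 0.05 and power to 80"%, "detection of a significant difference in resection ratios of 0.3", and a 4% margin for the two binary endpoints. It states no total sample size, SD or event rate.

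**The concern.** Resection ratio and re-excision depend on how the operation is done. The protocol admits operators of any experience at hospitals of differing volume, so it is reasonable to expect outcomes to vary by centre, though the protocol does not say that they do. Blocks drawn from a single list balance the arms overall but not within a hospital. The stated test then leaves centre variation in the error term.

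If the blocks run per centre, the allocation is balanced within hospitals but the stated test does not use that balance, so its standard error is slightly too large. Either way, precision is given up that a single model term could recover. Histology raises a similar point for re-excision, because the margin rule is stricter for pure DCIS.

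**Working it through.** The plan has no sample size or variance to reproduce, so the check is conditional on assumptions. From the documents come the target difference of 0.3, two-sided alpha 0.05, power 80% and the 4-point margin. Everything else below is assumed.

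**1. Scale of the trial.** For a difference of 0.3 the total before the 10% inflation is 126 at SD 0.6, 350 at SD 1.0 and 786 at SD 1.5. A total of 350 to 400 is used below.

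**2. Share of variance due to centre.** Assume centre shares of 45, 40 and 15% and mean ratios of 1.5, 1.6 and 2.1.
- Overall mean: 0.45 × 1.5 + 0.40 × 1.6 + 0.15 × 2.1 = 1.63.
- Between-centre variance: 0.45 × 0.13² + 0.40 × 0.03² + 0.15 × 0.47² = 0.041.
- Share f = 0.041 / (0.041 + within-centre variance), which is 3.9% at within-centre SD 1.0 and 10.2% at SD 0.6.

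**3. Power with centre in the model.** Take a design with 80% power unadjusted. Power = Φ[(1.96 + 0.842)/√(1 − f) − 1.96].
- f = 0.039: Φ(2.859 − 1.96) = 0.816.
- f = 0.102: Φ(2.957 − 1.96) = 0.84.

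A second set of assumptions (shares 50, 30 and 20%; centre means +0.3, 0 and −0.3; 175 per arm) gives f = 5.2% and power rising from 80.1% to 82.2%.

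**4. If lists do run per centre.** The unadjusted t-test then uses the total variance although the centre part has been balanced out. True two-sided alpha = 2Φ[−1.96/√(1 − f)].
- f = 0.039: 2Φ(−2.00) = 0.0455.
- f = 0.102: 2Φ(−2.07) = 0.039.

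Power of the unadjusted test is then Φ[0.842/√(1 − f)], or about 0.80 to 0.81, so adjustment still gains about 1 to 3 points.

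**5. Chance imbalance from one unstratified list.** In a simulation of blocks of 8 with 400 patients and the second set of centre assumptions, the 95th percentile of the absolute shift in the resection-ratio difference was 0.045. The target difference is 0.3 and the standard error about 0.10.

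For re-excision, assume 20 to 30% DCIS and rates of 30% in DCIS and 10% in invasive disease. The 95th percentile of the shift, at 350 to 400 patients, is 1.96 × 0.20 × √[4q(1 − q)/N], where q is the DCIS share.
- q = 0.2, N = 400: 1.6 points.
- q = 0.3, N = 350: 1.9 points.

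**6. What that shift means against the 4-point margin.** Overall re-excision is 0.2 × 30 + 0.8 × 10 = 14%, or 0.3 × 30 + 0.7 × 10 = 16%.
- Standard error at N = 350 to 400: √[4p(1 − p)/N] = 3.5 to 3.9 points, so a 95% half-width of 6.8 to 7.7 points.
- Share of that variance due to histology: q(1 − q) × 0.20² / [p(1 − p)] = 5 to 6%.
- Total needed for a 4-point margin (one-sided 0.025, 80% power): 4 × 2.802² × p(1 − p)/0.04² = about 2,360 to 2,640.
- Shift at that size, by the formula in step 5: 0.6 to 0.7 points, or 16 to 17% of the margin.

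**The case against.** A reader might infer that the trial is unstratified. The protocol does not establish that. It is silent, and envelopes with centre-prefixed codes are compatible with separate lists per hospital. What stands is that no stratification is stated and that the reader cannot tell which scheme is in use.

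A reader might also infer that all three primary tests ignore centre. Section 2.7 names tests only for continuous variables. Nothing stated for re-excision or sentinel node detection can be said to ignore centre, and their adjustment may sit in an analysis plan that is not shown.

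The most tempting stronger reading is that a chance imbalance in DCIS could decide the re-excision verdict, since 1.5 to 1.9 points is 38 to 48% of the 4-point margin. That does not hold. The shift is already inside the ordinary standard error. At 350 to 400 patients the interval is wider than the margin before any imbalance, and at a size able to test that margin the shift is about 0.6 to 0.7 points. Chance imbalance under randomisation costs precision; it is not bias.

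It is also fair to object that every size here rests on assumed inputs, that neither the PRECIS-2 table nor the margin definition reports outcome differences by centre or histology, and that the preoperative diagnosis need not match the pathology that determines which margin rule applies. Finally, section 8 carries an amendment dated April 2020 that addresses existing trial participants, so allocation was probably under way and stratification may no longer be open. The stated unadjusted test for the resection ratio survives all of these objections, and that can still be improved.

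**Conclusion.** The point holds as a modest loss of precision. Section 2.6 should say how the lists are organised, and the test fixed in section 2.7 for the resection ratio is less efficient than it need be.

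If centre explains about 4 to 10% of the variance in resection ratio, adjustment moves 80% power to about 82 to 84%. If lists run per centre, the stated t-test is slightly conservative, with alpha of about 0.039 to 0.046 instead of 0.05. These figures depend on assumed centre shares, centre means and SDs; with little difference between centres, the gain shrinks towards nothing. The validity of the comparison is not in question. The change is worth making because it is cheap.

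**What to change.** In section 2.7, compare the resection ratio with centre as a fixed effect, or with a centre-stratified rank test if the data are not normal. State that the re-excision and sentinel node detection risk differences will be adjusted for centre, for example by a Mantel-Haenszel stratified risk difference, with preoperative DCIS versus invasive histology added for re-excision. Fix this before any outcomes are examined by arm.

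In section 2.6, state whether lists run per centre. Only if allocation has not started, stratify by centre. Otherwise make the analysis change alone.

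The analysis change costs one or two model terms and no extra patients or procedures. Stratifying would leave some incomplete blocks. With a fixed block of 8 in an open-label trial, it would also make allocation within a centre somewhat easier to predict.
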